### Statistical analysis

For study question 1, the reduction of tremor due to PSA-DBS is calculated by subtracting the TRS score at baseline from the score obtained after the 2 months of continuous PSA stimulation (either 5MFU or 7MFU, depending on randomization).

As a secondary endpoint, the TRS score at 12 MFU under PSA stimulation is analyzed as a long-term parameter. Only some patients are stimulated in the PSA between 7MFU and 12MFU, since some patients might have chosen VIM stimulation after the randomization phase. Accordingly, a comparison between VIM and PSA stimulation at 12MFU might be possible (according to the group size).

For all other (secondary) endpoints evaluated for PSA-DBS, the difference between the score at 5/7MFU and the score at baseline is calculated.

For study question 2, the difference in tremor scores between PSA and VIM stimulation in each individual patient is calculated as the difference between TRS at 5MFU and 7MFU.

For all other (secondary) endpoints compared between PSA and VIM, the scores at 5MFU are compared with those at 7MFU, according to randomization group.

For study question 1, the mean reduction in tremor (TRS) due to PSA-DBS with its standard error and 95 % confidence interval is computed. The individual baseline and after-treatment values are tested against ”no reduction” using a paired *t* test. Similarly for SF-36, QUEST, and BDI-II, the mean change from baseline together with the corresponding 95 % confidence interval is calculated, and a paired *t* test is performed. A graphical display is used to examine the distribution of the data; in case of marked skewness or other non-conformity to test assumptions, the appropriate non-parametric tests are employed as a sensitivity analysis.

For study question 2, mean tremor at the end of the crossover period with PSA-DBS and VIM-DBS, respectively, is computed, with 95 % confidence intervals. A repeated measures analysis of variance, allowing for a period effect, is performed to quantify and test for a difference in mean tremor score between PSA and VIM in the crossover design. The mean difference between PSA and VIM with 95 % confidence interval is calculated from the model. Similarly for secondary outcomes, mean values under the two treatments are computed and compared using repeated measures analysis of variance.

All analyses are based on the intention-to-treat principle. Study question 1 is analyzed using the full analysis set including all randomized patients who begin PSA stimulation in the crossover period and who have a post-PSA stimulation evaluation. Study question 2 is analyzed using the crossover analysis set including all patients in the full analysis set who also begin VIM stimulation in the appropriate crossover period and who have a post-VIM stimulation evaluation. Additional analyses are performed on the per protocol set including all randomized patients who are eligible for the study according to all main inclusion/exclusion criteria and who are stimulated according to protocol in both crossover periods. Sensitivity analyses drop the requirement for post-stimulation examination data and instead impute any missing values (see below). The safety set includes all patients (randomized or not) who begin stimulation in any area (PSA, VIM, or ICL).

Since all patients included into the trial receive DBS electrodes, they are followed closely by our center for many years after the implantation. After completion of the study protocol, patients are seen at least every 6 months in our outpatient clinic. A careful evaluation and (if appropriate) adjustment of stimulation parameters usually leads to improvement of tremor suppression and quality of life. In the rare case of loss to follow-up, noncompliance, or revocation of study participation, the patient will be excluded from the per protocol analysis.

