## Methods

### Study design

The study design is illustrated in Fig. 1. After baseline evaluation, patients are implanted as described below (see study procedure). Three months post-implantation, patients enter a double-blinded crossover phase with VIM- and PSA-DBS in randomized order. After 7 months follow-up (7MFU), programming parameters are not restricted until termination of the study at 12MFU.

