Only if implantation criteria are fulfilled, i.e., both leads are placed as described above and proper lead location is confirmed via stereotactic X-ray or postoperative CT scan, are patients included at 3MFU into the double-blinded, randomized phase of the study. Patients are randomized into two groups (group 1: VIM-DBS followed by PSA-DBS; group 2: PSA-DBS followed by VIM-DBS). The crossover is double-blinded (neither the patient nor the treating neurologist knows which area is stimulated in which period) and lasts for 4 months (2 months on each treatment). A programming visit (PV) is performed at the beginning of each period (at 3MFU and 5MFU) and the best clinical stimulation parameters of the respective contact are determined (i.e., best tremor suppression with no or tolerable side effects). The stepwise increase of current of the electrode contacts in the crossover phase yields a better understanding of the therapeutic windows (i.e., range between effect and side effect) of the two target areas. Double-blinding is also maintained during the programming visit, as adjustment of stimulation parameters is performed by an independent investigator (programmer) as instructed by the blinded rater. An evaluation visit (EV) is performed after each group (EV1 at 5MFU and EV2 at 7 MFU). As the effects and side effects are known to be immediate (although not systematically investigated for VIM-DBS), a longer washout phase between the two crossover phases is not necessary. After the crossover phase, the contact with the best effect and fewest side effects or more complex stimulation paradigms (such as double monopolar or bipolar configurations) can be freely chosen for further treatment until 12MFU.

For study question 1, the change from preoperative to postoperative TRS during 2 months of PSA stimulation will be analyzed. Therefore, the data will be pooled from the EV at 5MFU and 7MFU depending on randomization.

Patients without electrode placement according to the implantation criteria (see above) but with electrodes bilaterally located in the PSA will be stimulated in the PSA directly after implantation, evaluated at 3MFU and 12MFU, and will be excluded from the comparison between PSA and VIM. For the longitudinal PSA effect, 3MFU data from these patients will be pooled with 5MFU and 7MFU data from the randomization group, respectively.

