### DBS programming

Directly after implantation and until 7MFU the activated electrode contact is determined by the study protocol (ICL, PSA, VIM or ICL, VIM, PSA), but the parameters can be freely chosen in terms of amplitude, frequency, and pulse width. However, all patients must be stimulated with constant current (mA), with a positive case and a single active cathode. In the crossover phase, at each programming visit, a monopolar review from 0 to 5 mA in 0.5-mA increments is performed. The amplitude with the best effect and fewest side effects is chosen for the final setting and is usually further adapted by the investigator during the programming visit before discharge. In general, a monopolar configuration with 60 μs and 130 Hz is chosen initially. In case a patient does not present a sufficient effect, the frequency and pulse width can be additionally modulated to improve the outcome.

If stimulation on a certain contact does not lead to a sufficient effect or intolerable side effects occur, and thus a change of the electrode contact or electrode configuration is inevitable, the corresponding crossover phase cannot be continued for ethical reasons. In this case the EV of the respective crossover phase must be performed immediately. After the end of the crossover phase, at 7MFU, the activated contact can be freely chosen.

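### The 12MFU results by stimulation site group patients by a contact chosen after 7MFU on its effect, so neither the long-term PSA score nor the optional PSA-VIM comparison is protected by randomization

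*Protocol article*

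**What the plan says.** The Statistical analysis section of the protocol article sets the long-term endpoint: "As a secondary endpoint, the TRS score at 12 MFU under PSA stimulation is analyzed as a long-term parameter". It says who will be in that group: "Only some patients are stimulated in the PSA between 7MFU and 12MFU, since some patients might have chosen VIM stimulation after the randomization phase". It then adds "Accordingly, a comparison between VIM and PSA stimulation at 12MFU might be possible (according to the group size". No other condition is attached, and no test is named for 12MFU.

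Three other places fix how the groups arise:

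- Study procedure: after the crossover the choice is open to "the contact with the best effect and fewest side effects or more complex stimulation paradigms".
- DBS programming: "After the end of the crossover phase, at 7MFU, the activated contact can be freely chosen".
- Study design: after 7MFU "programming parameters are not restricted until termination of the study at 12MFU".

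A further group never faces this choice. Under Study procedure, patients whose leads miss the dual-target criteria but lie bilaterally in the PSA "will be stimulated in the PSA directly after implantation, evaluated at 3MFU and 12MFU". Their 3MFU data are pooled into the longitudinal PSA effect. The article does not say whether their 12MFU data enter the long-term endpoint.

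The paragraph on analysis sets, at the end of Statistical analysis, states that every analysis follows intention-to-treat. It defines a full analysis set and a crossover analysis set, both by evaluations in the crossover periods. Neither is defined for 12MFU.

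**The concern.** By 7MFU each randomized patient has had about two months on each target, and the contact kept afterwards is picked largely on how tremor responded. Tremor is also what the TRS measures at 12MFU. Patients who did poorly on PSA tend to leave the PSA group, so the remaining mean describes patients content to stay on PSA, not PSA stimulation in the patients implanted.

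The PSA-VIM comparison sets two such groups side by side, each enriched for patients who did well on their own target. Larger groups would make that comparison more precise but no more valid. Patients on double monopolar or bipolar settings may fit neither group.

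Two things are at stake. A long-term PSA figure from a pilot meant to inform a larger multicentre trial could carry selection into that trial's planning. And a PSA-VIM contrast at 12MFU could be smaller than the randomized crossover result and be read as loss of a PSA advantage over time.

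**Working it through.** **The plan's own figure.** Sample size and power calculation gives n = 12 for a 9-point PSA-VIM difference (80 % power, 5 % level, correlation 0.5). A two-sided paired t test reproduces this with SD 10.1 for both values: SD of the difference = √(10.1² + 10.1² − 2 × 0.5 × 10.1 × 10.1) = 10.1, and power at n = 12 is 80.2 %. Dividing 12 by 0.8 gives 15. The point below does not depend on this figure.

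**Inputs for the illustration.**

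- From Sample size and power calculation: post-stimulation SD 8.8, correlation 0.5 between the two post-stimulation values, planning difference 9 points, planning reduction 46.2 − 18.7 = 27.5 points.
- Assumed: SD 8.8 under both targets, bivariate normal scores, and each patient keeping the contact with the lower TRS in the crossover.
- Assumed: a share q of the target-specific variance is stable to 12MFU. The documents give no value, so q runs from 0.25 to 1.

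**Formulas.** Let D be VIM minus PSA score in the crossover, with true mean d (positive means PSA is better).

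- SD of D = √(2 × 8.8² × (1 − 0.5)) = 8.8.
- Target-specific variance = (1 − 0.5) × 8.8² = 38.72. Divided by the SD of D, this is 4.4.
- With a = d/8.8, and φ and Φ the standard normal density and distribution function, the share choosing PSA is Φ(a).
- Shift of the PSA mean among PSA choosers = −4.4 q φ(a)/Φ(a).
- Shift of the VIM mean among VIM choosers = −4.4 q φ(a)/(1 − Φ(a)).
- Apparent contrast = d + VIM shift − PSA shift.

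**Targets truly equal (d = 0).** φ/Φ = 0.3989/0.5 = 0.798, so both shifts are −3.51 q and cancel in the contrast.

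**PSA truly 9 points better (d = 9).** a = 1.023, φ = 0.2365, Φ = 0.847. PSA shift = −4.4 × 0.279 q = −1.23 q. VIM shift = −4.4 × 1.543 q = −6.79 q. Apparent contrast = 9 − 5.56 q.

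| Stable share q | PSA overstated, d = 0 | Contrast, d = 0 | PSA overstated, d = 9 | Contrast, d = 9 |
|---|---|---|---|---|
| 0.25 | 0.9 | 0 | 0.3 | 7.6 |
| 0.50 | 1.8 | 0 | 0.6 | 6.2 |
| 0.75 | 2.6 | 0 | 0.9 | 4.8 |
| 1.00 | 3.5 | 0 | 1.2 | 3.4 |

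Simulation under the same assumptions agrees with these values.

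**Relative to the planning reduction.** 0.9/27.5 to 3.5/27.5 is about 3 to 13 % if the targets are equal. 0.3/27.5 to 1.2/27.5 is about 1 to 4 % if PSA is 9 points better.

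**Departures from the assumptions (simulated at q = 1).**

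- Unequal SDs: with 8.8 under PSA and 10.1 under VIM and no true difference, the contrast is about 2.1 points in favour of VIM. With the SDs swapped it is 2.1 points in favour of PSA.
- Choice also driven by other factors, such as side effects (added noise SD 8.8 to 17.6): PSA is overstated by about 1.0 to 2.5 points across true differences of 0 to 9, and a true 9 appears as 6.2 to 7.9.

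**Feasibility.** At d = 9 about 85 % choose PSA. Of 12 patients, 12 × (1 − 0.847) = 1.8 would be on VIM. Even with more even splits, an unpaired test of 9 points (SD 8.8) has power of about 36 % (6 and 6), 33 % (8 and 4) or 28 % (9 and 3).

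**The case against.** The strongest defence is that the text is open about the selection and modest in its claims. It says that only some patients will be on PSA and why, words the comparison as a mere possibility, and presents the study as a pilot needing confirmation. A 12MFU score under PSA is a fair description of patients maintained on PSA. The group-size condition would probably stop the comparison in the very case where it is most distorted. All of that stands, and it limits the weight of the point. It does not remove it: the long-term PSA endpoint is not hedged, group size says nothing about selection, and the limitations given in the Discussion do not mention it.

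Three stronger readings are tempting and are not supported:

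- **That both 12MFU estimates are necessarily biased.** With equal targets and equal SDs the contrast has no bias. With unequal SDs the sign can go either way. The largest overstatement of PSA and the largest shrinkage of the contrast also occur in different scenarios and should not be quoted together.
- **That the plan commits to a test at 12MFU.** None is named. The paired t test belongs to the 5/7MFU change and the repeated measures analysis to the crossover.
- **That every patient at 12MFU is on the contact that worked best.** Side effects also count in the choice, and patients with PSA-only placement never chose between targets.

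**Conclusion.** The point holds as a matter of design: both 12MFU by-site results rest on groups formed after randomization by response, and the only condition stated does not deal with that. Grouping by chosen contact also sits badly with the statement that all analyses follow intention-to-treat.

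In size, the overstatement of the long-term PSA effect is small beside the planned reduction. The possible distortion of the contrast is larger: more than half of a true 9-point difference could vanish if target-specific response is fully stable. These figures rest on normal scores, choice by TRS alone and an assumed stable share, so they show scale and are not predictions. The primary endpoint and the randomized 5MFU/7MFU comparison are untouched. This should be corrected, but it does not threaten the trial's main conclusions.

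**What to change.** Change the wording of the analysis plan only:

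1. Add, as the 12MFU analysis, the change in TRS from baseline in all randomized patients under whatever setting is in use.
2. Report the proportions on PSA, VIM and combined settings at 12MFU.
3. Keep 12MFU TRS by chosen site, including the score under PSA, but label it descriptive and non-randomized, with no PSA-VIM inference.
4. Show patients with PSA-only lead placement separately, since they were not randomized and did not choose between targets.
5. Reconcile the 12MFU paragraph with the intention-to-treat statement by naming the analysis set used at 12MFU.

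No visit, measurement or treatment changes. The cost is giving up any inferential long-term claim about PSA alone, or about PSA against VIM, at 12MFU.

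### The only per protocol set requires adherence in both crossover periods, so a VIM-period deviation can remove a valid PSA-versus-baseline pair from the supplementary analysis of question 1

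*Protocol article*

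**What the plan says.** All references are to the protocol article.

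- **Main set, question 1** (Statistical analysis): the full analysis set, "all randomized patients who begin PSA stimulation in the crossover period and who have a post-PSA stimulation evaluation". It carries no VIM condition.
- **Main set, question 2** (Statistical analysis): the crossover analysis set, "all patients in the full analysis set who also begin VIM stimulation in the appropriate crossover period", with a post-VIM evaluation as well.
- **Per protocol set** (Statistical analysis): "Additional analyses are performed on the per protocol set including all randomized patients who are eligible for the study" by the main criteria and "who are stimulated according to protocol in both crossover periods". No second version is given, and the additional analyses are not tied to either question.
- **Named per protocol exclusions** (Statistical analysis): "In the rare case of loss to follow-up, noncompliance, or revocation of study participation, the patient will be excluded from the per protocol analysis".
- **Question 1 endpoint** (Statistical analysis): the change from baseline to the "score obtained after the 2 months of continuous PSA stimulation (either 5MFU or 7MFU, depending on randomization").
- **Early end of a phase** (DBS programming): if a contact has insufficient effect or intolerable side effects and must be changed, "the corresponding crossover phase cannot be continued for ethical reasons". The rule continues: "In this case the EV of the respective crossover phase must be performed immediately".

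**The concern.** The main sets recognise that question 1 does not depend on the VIM period. The per protocol definition drops that distinction. Adherence in the VIM period is a post-randomization event that is no part of the PSA-versus-baseline contrast. In the PSA-VIM order it occurs after the PSA value has been recorded at 5MFU, so a later deviation would remove a pair that was already complete and conforming.

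Two things are at stake in the per protocol check on the primary endpoint. The first is precision, because the trial plans for only 12 evaluable patients. The second is selection. Both contacts sit on the same lead, so patients who do badly on VIM may also respond less well to PSA. Leaving them out would then make the PSA effect look larger than it is among all patients who adhered to PSA.

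**Working it through.** **1. Which data each analysis needs**

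| Analysis | PSA period | VIM period |
|---|---|---|
| Question 1, main | begun and evaluated | not required |
| Question 2, main | begun and evaluated | begun and evaluated |
| Per protocol (one set) | according to protocol | according to protocol |
| Question 1 endpoint itself | post-PSA score and baseline | not used |

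The third row matches the needs of question 2 but asks more than question 1 uses.

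**2. Inputs** (Sample size and power calculation): SDs 10.1 and 8.8; correlation 0.5; expected reduction 46.2 − 18.7 = 27.5 points; 12 evaluable patients; 15 recruited.

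**3. The plan's own figures** (exact paired t test, two-sided 5%)

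- SD of the change for question 1 = √(10.1² + 8.8² − 2 × 0.5 × 10.1 × 8.8) = 9.52.
- Question 1: power for 27.5 points is 0.720 at n = 3 and 0.957 at n = 4, so n = 4 reproduces.
- Question 2: 9 points with an SD of the difference of 10.1 gives power 0.802 at n = 12, so n = 12 reproduces.
- Recruitment: 12 / 0.8 = 15 reproduces.
- The 9.7 points said to be detectable at n = 12 does not reproduce with SD 9.52, which gives 8.46; it would need an SD of about 10.9. This does not bear on the present point.

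**4. Precision lost** (half-width = t(0.975, n−1) × SD / √n)

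- n = 12: 2.201 × 9.52 / √12 = 6.05 points.
- n = 10: 2.262 × 9.52 / √10 = 6.81 points.
- n = 8: 2.365 × 9.52 / √8 = 7.96 points.

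Losing 2 of 12 widens the interval by 6.81 / 6.05 = 1.13, about 13%. That ratio does not depend on the SD. Power for 27.5 points is still 0.9998 at n = 6.

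**5. How many patients might be affected**

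The article gives no rate of early-ended phases. Assume 15 randomized patients, the same probability p in each period, independence between periods, every early-ended phase counted as off protocol, and the other period still carried out. The shared set then has expected size 15(1−p)², and a PSA-only set 15(1−p).

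| p | Shared set | PSA-only set | Lost only because of VIM |
|---|---|---|---|
| 0.05 | 13.54 | 14.25 | 0.71 |
| 0.10 | 12.15 | 13.50 | 1.35 |
| 0.20 | 9.60 | 12.00 | 2.40 |
| 0.30 | 7.35 | 10.50 | 3.15 |

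If failures cluster within patients, fewer are lost because of VIM alone.

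**6. Possible selection**

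Suppose 2 of 12 PSA-adherent patients are lost because of VIM and their mean PSA reduction is 9 points smaller than that of the other 10. The 9 points are borrowed from question 2 purely as an illustration. The mean over 12 is then lower than the mean over 10 by 2 × 9 / 12 = 1.5 points. If their response does not differ, there is no shift.

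**The case against.** **Does a stopped VIM phase remove the patient?** A reader might infer that it does. The text does not fix this. Ending the phase and evaluating at once are themselves protocol rules, so a patient handled that way can be read as stimulated according to protocol. The named exclusions (loss to follow-up, noncompliance, revocation) do not include such a phase. Against that, Study procedure specifies 2 months on each treatment, so the opposite reading is equally open. This objection stands: for stopped phases the defect is an ambiguity. For other VIM-period deviations, such as noncompliance, the removal follows from the definition.

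**Does the set apply to question 1 at all?** The article does not say so. The sentence follows the main sets for both questions without restriction, so applying it to both is the natural reading, but it remains a reading.

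**Is the PSA pair always complete?** Only clearly so when PSA comes first. If VIM comes first and is stopped, the article does not say whether the PSA period follows.

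**Is the PSA effect therefore inflated?** A reader might conclude this from the shared lead. The documents do not support it. A patient who fails at both contacts would leave a PSA-only set too, so only patients who fail on VIM and complete PSA can shift the estimate, and nothing shows that they respond less to PSA. Lead position is also confirmed before randomization.

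**Is one set a legitimate choice?** It has a rationale, since both questions are then checked in the same adherent patients. Detailed deviation rules may also sit in an analysis plan that is not shown. The requirement of both periods, however, is stated in the article, and it departs from the logic of the article's own main sets.

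**Conclusion.** The point holds as a small improvement to a stated rule. There is one per protocol set, it requires both periods, and question 1 needs only one of them. Used for question 1, it can drop conforming PSA-versus-baseline pairs for reasons unrelated to that endpoint.

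A reader might also infer that the primary analysis loses patients or power. It does not: the full analysis set has no VIM condition, and a stopped VIM phase leaves the patient in it. The half-width of 6.81 rather than 6.05 points is modest beside an expected reduction of 27.5 points, and the conclusion on question 1 is unlikely to change.

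The size rests on the article's SDs and correlation and on an assumed loss of 2 of 12. Any selection effect is possible but undemonstrated.

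**What to change.** In the Statistical analysis section or the analysis plan:

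1. Define the per protocol set by question. For question 1: eligible randomized patients stimulated according to protocol in the PSA period, whatever happened in the VIM period. For question 2: adherence in both periods, as now.
2. State whether a phase ended under the DBS programming rule counts as according to protocol, so that the two sections are reconciled before unblinding.

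This takes a sentence or two and no extra data. The only drawback is two per protocol sets of slightly different size, which need separate labels in the report.

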### Study procedure

Patients are screened for study participation and implanted with DBS systems capable of current-controlled (mA) stimulation (Activa RC/PC, Medtronic or Vercise System, Boston Scientific) in the VIM and PSA bilaterally within 6 weeks of study enrollment. Both leads are implanted so that each lead has at least one contact inside the PSA, one inside the VIM, and one ”neutral contact” located on the intercommissural line (ICL, line connecting the anterior with the posterior commissure) in between the two target areas. Between implantation and randomization at 3MFU, this neutral contact is activated and adjusted for optimal tremor suppression with minimal side effects. This is done to ensure that all patients receive the same type of stimulation before entering the randomization phase of the study.

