### Outcome measures

The primary endpoint of this study is the reduction of tremor, measured via a reduction in TRS scores, due to PSA-DBS over 2 months compared to preoperative baseline. The TRS is a widely used and well-accepted scale for the clinical assessment of tremor and has been used in most controlled ET studies. The scale was first published in 1993 [24] and validated for ET in 2007 [27]. It consists of three parts: (A) tremor assessment, (B) task assessment, e.g., pouring water from one glass into another, writing, drawing spirals, and (C) a questionnaire assessing activities of daily living, e.g., eating soup with a spoon, social distress, hygiene; the different parts reflect the impairment due to tremor in different dimensions. The TRS has also been used as the primary endpoint measure in the retrospective analysis of Blomstedt et al. [13], which is the basis of power calculation for our study.

Secondary endpoints comprise general (SF-36 [25]) and disease-specific quality of life (QUEST [4], non-validated German version), depression (Beck Depression Inventory, BDI-II [28]), ataxia (International Cooperative Ataxia Rating Scale, ICARS [29]), and the patients’ and physicians’ subjective impressions on tremor severity and side effects (gait and speech) measured via visual analog scale (VAS). Stimulation-induced side effects are determined and recorded as adverse events throughout the study.

In addition, the amount of electric current applied during adjusted stimulation comprises a further endpoint. In case no difference in efficacy is seen between PSA and VIM stimulation in the crossover phase, it is particularly important to detect whether PSA stimulation requires less current on average and if the side effect profile differs in contrast to VIM stimulation. An acoustic speech sample is collected at each visit. The samples are analyzed by a phonetician and speech therapist as previously described [10, 30].

Together, these instruments provide a comprehensive assessment of subjective and objective treatment effects beyond mere motor effect.

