### Implantation procedure

The general surgical procedure has been published in detail before. Patients are operated under local anesthesia with sedation (remifentanil and propofol).

In summary, after fixation of the stereotactic frame (CRW Stereotactic System, Integra Neurosciences, or Riechert-Mundinger frame), planning is performed on fused stereotactic CT/MRI images, with the Framelink (Medtronic Inc.) or STP 3.5 (Leibinger) planning station.

The trajectory is planned so that both VIM and PSA can be stimulated, with one electrode contact on the AC-PC level. Macrostimulation is performed in all patients. Microrecording is selected in a number of patients based on the surgeon’s preference. Implanted electrodes are quadripolar electrodes from Medtronic Inc. (model 3387 or 3389) or octopolar electrodes from Boston Scientific (model 616010).

Finally, the pulse generator (Activa PC, model 37601; Activa RC, model 37612, Medtronic, USA or Vercise, Boston Scientific, USA) is implanted subcutaneously in the infraclavicular or lateral abdominal region under general anesthesia.

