### Safety

Implantation of electrodes in the PSA has so far not been associated with a higher risk for complications in these patients.

Adverse events (AEs)/serious adverse events (SAEs) are documented at the scheduled and unscheduled clinical visits. All incidents are reported to the regulatory authority. All safety-relevant events are promptly reported to the ethics committee and the safety monitor ([name], Department of Stereotactic Neurosurgery, University of Magdeburg, Germany).

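### The safety set starts at first stimulation, so a patient who is operated on but never switched on belongs to no analysis set

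*Protocol article*

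**What the plan says.** The Statistical analysis section of the Protocol article gives the definition: "The safety set includes all patients (randomized or not) who begin stimulation in any area (PSA, VIM, or ICL"). Randomization is waived as an entry condition; the start of stimulation is not.

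Surgery comes first and belongs to the study. Study procedure has systems implanted "in the VIM and PSA bilaterally within 6 weeks of study enrollment". Implantation procedure shows that the design shapes the operation: "The trajectory is planned so that both VIM and PSA can be stimulated". Activation is a later step, described in DBS programming: "Directly after implantation and until 7MFU the activated electrode contact is determined by the study protocol". Statistical analysis also notes that surgery reaches everyone included: "Since all patients included into the trial receive DBS electrodes, they are followed closely by our center".

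On safety data, Outcome measures concentrates on stimulation ("Stimulation-induced side effects are determined and recorded as adverse events throughout the study"), while the Safety section collects events without reference to stimulation: "Adverse events (AEs)/serious adverse events (SAEs) are documented at the scheduled and unscheduled clinical visits". That section also treats implantation risk as a safety topic, summarising past experience: "Implantation of electrodes in the PSA has so far not been associated with a higher risk for complications in these patients".

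**The concern.** The patient is exposed to the risks of bilateral intracranial surgery and generator placement before the entry condition of the safety set can be met. For anyone who goes on to activation this makes no difference. It matters only for patients operated on and never switched on, and a serious surgical complication is an obvious reason for that to happen. Membership of the safety set can therefore depend on a consequence of the study procedure.

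What is at stake is whether a table of procedure-related events built on this set would be complete. In a pilot with a recruitment target of 15, one omitted patient is the difference between an event observed and none observed.

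**Working it through.** No figure in the article is in dispute. The check is of the definition, followed by an illustration of size.

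**Step 1: order of events.** From Study procedure, Implantation procedure and DBS programming: enrolment, then implantation, then activation of a contact (the neutral contact for patients placed as planned; PSA directly for those with only bilateral PSA placement), then randomization at 3 months for those meeting the placement criteria. The safety set opens at the third of these steps for a patient placed as planned, while exposure to the procedure begins at the second.

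**Step 2: does another set pick up a never-activated patient?**

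| Set | Entry condition (paraphrased) | Never-activated patient included? |
|---|---|---|
| Full analysis | Randomized, began PSA stimulation in the crossover, evaluated afterwards | No |
| Crossover | In the full analysis set, and likewise for VIM | No |
| Per protocol | Randomized, eligible, stimulated per protocol in both periods | No |
| Safety | Began stimulation at any site | No |

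The sensitivity analyses relax only the need for post-stimulation data, so they do not bring such a patient back. The non-randomized patients pooled for the longitudinal PSA effect are stimulated by definition.

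**Step 3: who is affected.** Patients placed as planned, and those with bilateral PSA placement only, are all meant to be activated. Surgical harm in any of them stays in the set once stimulation starts. The set differs from one based on implantation only by patients never activated. The article describes no path for implanted patients meeting neither placement condition; if any were never stimulated, they would fall outside too.

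**Step 4: illustration of size.** Inputs:

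- Denominator: 15, the target recruitment in Sample size and power calculation, which reproduces as 12 / (1 − 0.20) = 15. That all 15 are implanted is an assumption.
- Number of never-activated patients with a surgical complication: assumed 1, then 2, with no such complication in the others. The article gives no surgical risk.

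Exact (Clopper-Pearson) 95% limits. For 0/n the upper limit is 1 − 0.025^(1/n); for 1/n the lower limit is 1 − 0.975^(1/n). The remaining limits are beta quantiles.

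- 0/14: upper limit 1 − 0.025^(1/14) = 23.2%.
- 1/15: lower limit 1 − 0.975^(1/15) = 0.2%; upper limit 31.9%.

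| Assumed cases | Implantation begun | Set as written |
|---|---|---|
| 1 | 1/15 = 6.7% (0.2% to 31.9%) | 0/14 = 0% (0% to 23.2%) |
| 2 | 2/15 = 13.3% (1.7% to 40.5%) | 0/13 = 0% (0% to 24.7%) |

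**Step 5: how likely is at least one such patient?** With per-patient risk p, the chance among 15 is 1 − (1 − p)^15. For assumed p of 1%, 2% and 5%:

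- 1 − 0.99^15 = 14%
- 1 − 0.98^15 = 26%
- 1 − 0.95^15 = 54%

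These risks only show a range; none comes from the document.

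**The case against.** The defence has real force on four points.

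- **Purpose.** The stated safety interest is in stimulation effects at two sites, in both Outcome measures and the Discussion. For that question, patients who began stimulation are the right denominator. A reader might infer that the plan will report a surgical complication rate biased downward. The article does not support this: it lists no such rate as an endpoint and does not plan to estimate one.
- **Capture.** A reader might also infer that such events vanish. They do not. The Safety section has events documented and incidents and safety-relevant events passed on to the authority, the ethics committee and the safety monitor, with no condition on stimulation. Withdrawal from the study adds a documented reason and a final examination.
- **Breadth.** The set is otherwise wide: any site, including the neutral contact, and randomized or not. Only patients never activated are lost.
- **Size.** The illustration rests on an assumed event, its two intervals overlap heavily, and 15 patients cannot estimate a surgical risk usefully under either definition.

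The sentence on past experience with PSA implantation is background, not an analysis rule, and does not conflict with the definition. How events in never-stimulated patients are listed or narrated may also be settled in documents not shown.

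All of this limits the consequence. It does not remove the gap: the definition is stated, surgery is a study procedure, and no other set covers the patient. An interest in stimulation effects justifies a stimulated subset, but not making that subset the whole safety population.

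**Conclusion.** The point holds as a gap in the safety set definition that should be fixed. Followed as written, the rule places an implanted but never-activated patient outside every analysis set, so a summary of procedure-related events drawn from the safety set could omit that patient's event. With one assumed case among 15 implanted, the contrast is 0/14 against 1/15; whether any case occurs is unknown, since the article gives no surgical risk.

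The documents support neither a finding of a biased complication rate nor one of unreported harm. The primary endpoint, the crossover comparison and the sample size are unaffected.

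**What to change.** Define the safety set as all enrolled patients in whom implantation was begun, whether or not stimulation followed, and use it for procedure-related events. Keep the patients who began stimulation as a named subset, used to tabulate stimulation-induced side effects by site.

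This is a one-sentence change to the analysis-set definitions, best made before the analysis. It needs no extra visits or data, because the Safety section already has adverse events documented at scheduled and unscheduled visits. The one small downside is that the reported safety result may become less favourable.
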